#### Primary outcome: physical activity level

3.7.1

ActiGraph wGT3X-BT accelerometers and the ActiLife 6 (United States) software will be used to measure the children’s level of physical activity. This device has proven validity and reliability to objectively measure the level of physical activity in children (38–40). The physical activity level will be only monitored during the school day.

#### Secondary outcomes: on-task classroom behavior

3.7.2

Information will be compiled on the behavior of the students in the classroom individually using the Direct Behavior Rating Scale (41), and they will also be measured as a group by applying a modified version of the Classroom Behavior and Assets Survey-Teacher, which is designed to efficiently evaluate the teacher’s perception of the behavior of all the students in a class.

#### Secondary outcome: physical activity enjoyment

3.7.3

The Physical Activity Enjoyment Scale (PACES) (42) will be individually applied to the participants. This is a scale that has reported good reliability in children (Cronbach’s alpha of 0.96) (43), and it has even been used in other studies with this population (44, 45). The questionnaire will be applied referring to “when I participate in the active breaks…”.

Physical activity: ActiGraph wGT3X-BT accelerometers and the ActiLife 6 software will be used to measure the children’s level of physical activity, since this device is proven to have the validity and reliability to measure the physical activity level objectively in this age group (38). The accelerometers will be used during the school day prior to the intervention, in weeks 1, 3 and 6, in both the intervention and control groups. The accelerometers will be handed out and collected from the child at school at the beginning and end of each school day.

The accelerometers will be placed at the beginning of every school day, since the device is programmed and activated by an internal clock from the software so that it begins to record for the established time. The accelerometers are placed using an elastic belt at the intersection of the right hip and waist (on the iliac crest), as this is the place next to the center of gravity (39). Data from the participants who do not fulfill what is requested for the recording (days and hours) will not be analyzed. A short duration epoch of 15 s will be used; because the pattern, more intermittent the children’s physical activity (46), frequency of 100 Hz. The classification of the daily level of physical activity will be: sedentary, light, moderate, vigorous and moderate-vigorous, established from counts per minute. The cut-off point used will be determined by Evenson’s equation for the ActiGraph wGT3X-BT, especially used for students’ task classroom behavior (47) (sedentary 0–100 counts^x^min^−1^, light 100–2,295 counts^x^min^−1^, moderate 2,296–4,012 counts^x^min^−1^, vigorous 4,013 counts^x^min^−1^).

On-task classroom behavior: Information will be compiled on the students’ behavior in the classroom individually and as a group. The observation will be done in weeks 1, 3 and 6, in the intervention and control groups. The members of the research team trained in the data collection instrument will make observations on the students’ behavior during a period of 15 min before and after participation in a break with ACTIVA-MENTE.

Individual classroom behavior will be measured using a tool adopted from the Direct Behavior Rating Scale (41). The Direct Behavior Rating Scale is a hybrid of behavior grading scales and direct observation. This observation tool requires the teacher to indicate for each child, on a scale from 1 (0%) to 10 (100%), the percentage of time they spend on the task, i.e., how committed they are to the task (e.g., listening to the teacher, writing, looking at instruction materials, etc.) during the observation period. This tool has evidence of reliability (r = 0.91) based on data from 617 elementary students from 44 classroom teachers (41).

Group behavior, otherwise, will be measured using a modified version of the Classroom Behavior and Assets Survey-Teacher, which is designed to provide the teacher’s perception of students’ behavior in class. The member of the research team trained in the instrument will indicate the proportion of the class that shows on-task behavior (as defined in the individual behavior assessment tool) during the observation period. The response options include: 0 (0 students), 1 (1–2 students), 2 (some students), 3 (approximately one quarter of the class), 4 (approximately half the class), 5 (approximately three quarters of the class), 6 (most of the class) and 7 (the entire class). Although there are few tools available to evaluate classroom behavior at class level, and a lack of information on reliability and validity, a modified version of this tool was used in a similar study, with evidence of reliability (alpha = 0.85) (13).

Physical activity enjoyment: The PACES will be applied in the weeks 1, 3 and 6, to the intervention group. PACES will be applied to the participants individually (42). This is a scale that has reported a high reliability in children (Cronbach’s alpha of 0.96) and it has even been used in other studies with children (45, 48). PACES consist of 16 items rated from 1 to 5, with 1 being “strongly disagree” and 5 being “strongly agree.” For example, positive items referred to statements such as “I enjoy it,” “I find it pleasurable,” and negative items had statements such as “I dislike it” or “It’s no fun at all.” The questionnaire will be applied referring to “when I participate in the active breaks…”.

As a general following up of the intervention, questionnaires will be used to collect information on the acceptability of the program by the directors, teachers and students in each school. They will be asked to report the facilitators and barriers to the implementation of ACTIVA-MENTE, as well as to suggest which component could be improved for implementation on a wider scale. Study participants will be asked about unexpected outcomes of the intervention. The field team will record positive and negative factors that affect the implementation to be able to optimize future interventions. This process will be done through semi-structured observations, where the research team will document the measured duration and fulfillment of the activities, the dynamic in the class or the activity, spaces, and others.

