### Study design

3.1

The study is carried under a quantitative method. This study uses an experimental design with a pre-and post-test. The sample will be divided into two groups: intervention and control. An active break program - ACTIVA-MENTE – will be applied to the intervention group in their respective classes during the school day for 6 weeks, while the control group will perform their regular school day (without any intervention).

The protocol was developed in agreement with Standard Protocol Items: Recommendations for Interventional Trials (SPIRIT) and according to the verification guidelines of Consolidated Standards of Reporting Trials (CONSORT). Figure 1 provides a general description of the chronogram of enrolment, interventions and assessments.

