One week before implementing the program, all the teachers will be trained for 45 min. The training session will be carried out in the schools by a researcher, who is a qualified elementary school teacher. The training session is designed to inspire and instruct the teachers with the necessary skills and knowledge to implement the ACTIVA-MENTE program. This training session content will include the importance to add physical activity times into the classroom routine; the evidence of current research that emphasizes the potential positive effect of active breaks to improve the physical activity levels and the on-task behavior; the explanation regarding the program; and finally, the instructions for program application. Since a researcher will be present during the first 2 weeks of implementation, extensive demonstrations of the active break activities will not be provided during the training session. After training session, the printed and the digital materials of ACTIVA-MENTE will be distributed, as well as a certification.

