### Procedures, outcomes measures and data collection

3.7

Three measurements will be assessed at weeks 1, 3 and 6: physical activity levels, on-task classroom behavior and enjoyment of physical activity. The implementation will be carried out by a group of research collaborators properly trained by the research team during four sessions previous to the assessment on the application of the instruments. The evaluators do not know the students and in the research, they only carry out the data collection.

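### On-task behavior is timed around a break that control classes never have, and two different raters are named for the individual rating

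*Protocol article*

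**What the plan says.** The operational description of on-task behavior stands in the protocol article under section 3.7.3, after the accelerometer paragraphs.

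- **Who is observed, and when:** "The observation will be done in weeks 1, 3 and 6, in the intervention and control groups".
- **Window:** "during a period of 15 min before and after participation in a break with ACTIVA-MENTE". No other anchor is given for either group.
- **What controls receive (section 3.1):** "the control group will perform their regular school day (without any intervention").
- **Rater, first statement:** "The members of the research team trained in the data collection instrument will make observations on the students’ behavior".
- **Rater of the individual scale, second statement:** "This observation tool requires the teacher to indicate for each child, on a scale from 1 (0%) to 10 (100"%).
- **Rater of the group scale:** "The member of the research team trained in the instrument will indicate the proportion of the class that shows on-task behavior".
- **Evaluators in general (section 3.7):** "The evaluators do not know the students and in the research, they only carry out the data collection".
- **Teacher training (section 3.6):** the session covers research that "emphasizes the potential positive effect of active breaks to improve the physical activity levels and the on-task behavior".

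Section 3.10 then compares the groups on mean outcome scores over the intervention period, on-task behavior included, with adjustment for the baseline of each variable.

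**The concern.** Two instructions cannot be carried out as written.

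First, a window defined by a break is applied to an arm without breaks. Someone in the control school must choose when to watch. If the chosen minutes fall elsewhere in the lesson, ordinary changes in attention over a lesson enter the difference between arms and look like a programme effect, or hide one.

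Second, the individual rating has two named raters. If the research team rates, the same people can score both schools. If teachers rate, each teacher scores only one arm, because section 3.2 plans one school per arm. The intervention teachers run the breaks themselves and have been told what benefit to expect. An upward shift in their scoring could not then be separated from a true effect.

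Neither problem can be repaired in the analysis once the observations have been made.

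**Working it through.** The plan attaches no figure to this outcome, and its one calculated design figure (54 students, section 3.3) does not bear on the point. The check is a comparison of sections plus one timing calculation.

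**1. Does the control window exist?** Section 3.7.3 requires observation in both groups and anchors it to an ACTIVA-MENTE break. Section 3.1 gives controls no intervention. No matched lesson time or sham time point is stated, so the control window is not defined.

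**2. Could it be defined from the plan's own figures?** Inputs from section 3.5: class of 45 min, break at minute 20, video of 4 min 30 s (4.5 min). Input from section 3.7.3: 15 min on each side.

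- Before: 20 − 15 = 5, so minutes 5 to 20.
- Break: 20 + 4.5 = 24.5, so minutes 20 to 24.5.
- After: 24.5 + 15 = 39.5, so minutes 24.5 to 39.5.
- Fit: 39.5 ≤ 45, with 45 − 39.5 = 5.5 min to spare.

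Both windows fit inside the lesson, so the same clock can be used in control classes.

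**3. Who rates?**

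| Measure | Rater stated | Consistent? |
|---|---|---|
| On-task observation in general | Trained research-team members | – |
| Individual scale | Teacher | No: conflicts with the row above, and with section 3.7, since a class teacher knows the pupils |
| Group scale | Research-team member | Yes, although the source instrument is described as capturing the teacher's view |

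The conflict is therefore confined to the individual scale.

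**4. What follows if teachers rate?** Section 3.6 has the classroom teacher leading the breaks, alone from week 3, after training on their expected on-task benefit. With one school per arm, rater and arm coincide. The documents give no figure for the resulting bias.

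**5. Which score is compared?** Section 3.7.3 collects a before and an after window. Section 3.10 does not say whether the before score, the after score or the change enters the model.

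**6. Is there a baseline?** Section 3.10 adjusts for one. The on-task paragraphs list only weeks 1, 3 and 6, all within the intervention period.

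**The case against.** The best defence is that this is a condensed article and the intention can be guessed. The mid-lesson rule in section 3.5 suggests an obvious clock match for controls. The individual tool is introduced as adapted from a published scale, so the sentence about the teacher may describe that source instrument. The group-scale paragraph follows the same pattern: it describes a teacher-perception instrument and then names a research-team rater. Section 3.7 also has trained outside evaluators doing the assessments. Finally, baseline adjustment would remove at least part of any constant leniency.

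Much of this is fair, and research observers are the more likely intention. But the article does not say so. It states a break-anchored window for both groups and names the teacher as scorer. These are conflicting statements, not details left to a fuller document. Baseline adjustment needs a rating taken before the programme starts, and none is listed. Even with one, a shift in scoring that begins with the intervention would remain.

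Three stronger readings are tempting but not supported:

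- *The analysis pools the before and after windows and so halves an acute effect.* Section 3.10 speaks of averages over the intervention, most naturally across weeks 1, 3 and 6. It does not say that the windows are averaged. Halving would also require equal weights and no effect in the before window. With six breaks a day, that window may already carry effects of earlier breaks.
- *Teacher leniency would add about 11 percentage points.* One step on the 1–10 scale is 100/9 = 11.1 points, but that is the size of a scale step, not an estimate of bias. It matters only if teachers rate and their leniency differs between arms.
- *The arm contrast as a whole is undefined.* Section 3.10 does name a group comparison. What is open is the control window and which window's score is used.

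**Conclusion.** The point holds in a limited form. The control observation window has no anchor, and the rater of the individual scale is contradictory. Both rest on the text alone. Expectation bias confounded with arm is a supported risk, conditional on teachers doing the rating, and its size is unknown. Distortion from unmatched lesson times is likewise conditional on when controls are actually watched.

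The scope is a secondary outcome. It is named in the study aim, so it should be settled before data collection. The accelerometer primary outcome is not touched. The rater conflict does not extend to the group scale, whose rater is stated, but the missing control window affects both scales.

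**What to change.** 1. State that trained research observers give the individual ratings in both schools, with the same observers covering both where feasible. Treat any teacher ratings as supportive only.
2. Fix the control windows to the same lesson clock as the intervention classes: about minutes 5–20 and 24.5–39.5 for a 45-minute class with the break at minute 20.
3. State which window's score enters the section 3.10 comparison.
4. Adjust only for an on-task baseline observed before the intervention, and schedule that observation if it is not already planned. Do not adjust for the same-day before-break window. It is measured after randomization, and earlier breaks may already have affected it. Conditioning on it could remove a sustained effect and would change the question to the acute effect of one break.

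The cost is wording, observer scheduling and travel between schools. The six research collaborators in section 3.9 are already planned, and any added baseline round would need their time. Two limits remain: observers present around a break can see the arm, so they are not blinded, and with one school per arm, school differences stay confounded with the intervention whoever rates.

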### Ethics and dissemination: research ethics approval, consent and confidentiality

3.8

The study is designed according to the international ethical standards of the Declaration of Helsinki and was approved by the Scientific Ethics Committee of the Universidad de Playa Ancha (N° 005–2022). In addition, it follows the ethical standards for physical activity sciences and sports (49). A complete assessment about the protocol will be delivered to the parents or guardians and students during the study.

The parents or guardians will sign an informed consent allowing the students participation in the study. The students will also sign an assent form confirming they want to participate the study before the intervention be implemented.

Before, during and after the intervention and data collection, the potential participants’ personal information will be fully protected and will only be used for research purposes and dissemination of knowledge.

### Data management, data access and dissemination policy

3.9

Data will be collected in the schools that are part of the study. This process will be done by a group of six research collaborators, who will provide the collected data to the principal investigator and to the co-investigator who will introduce them into two databases: Redcap and Dropbox. Then, the ordered data will be exported to a statistics program to execute the respective analyses.

The researchers responsible for this study will have access to the data. The anonymized data set will be at the disposal of the collaborating researchers and peer reviewers who require them through a virtual folder in the Dropbox application.

Once the study is finished, the results will be shared nationally via digital platforms (Webinar) of the Chilean Ministry of Education and internationally through conferences and seminars. For dissemination to the entire scientific community, articles will be published in scientific journals of the area.

### Statistical analysis

3.10

All the statistical analyses will be performed using jamovi software (50). The data will be reported as the mean and standard deviation for both experimental and control groups. Multilevel mixed-effects linear regression models will be used to assess the impact of the group (intervention vs. control) on the average scores of the physical activity level, on-task behavior and enjoyment of physical activity during whole intervention. Each variable will be fit by baseline levels of the corresponding variable and grouping by classes. All the analyses will control for the levels of physical activity at the beginning. All the analyses will be stratified by sex. We will consider the results statistically significant only if the *p* value will be lower than 0.05. We will calculate the effect size to examine the magnitude of any mean differences.

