**Methods:**

The protocol includes children aged 10 to 11 years. Two groups will be randomized (intervention and control groups). The intervention group will use the active break program, ACTIVA-MENTE, which consists of the application of a 4-min, 30-s video with moderate to vigorous-intensity physical activity. These breaks will be taken 6 times a day in the classes for 6 weeks. The total physical activity will be measured with accelerometers (Actigraph wGT3X-BT), the on-task behavior through the Direct Behavior Rating Scale and the level of enjoyment through the Physical Activity Enjoyment Scale.

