### Study sample

3.2

The study will be conducted at elementary schools in Valparaíso, Chile, from a low to middle low socioeconomic level (C_3_-D, respectively) (29). This group was selected in attempt to get a representative sample, since most of the Chilean population are classified with these socioeconomical level (29). The study sample consists in students of 10 to 11 years of age. The students who attend these schools spend approximately 8 hours a day at school (from 8:00 a.m. to 4:00 p.m.) with two recesses of approximately 15 min each (30 min altogether) and a longer rest for lunch of between 45 min and 1 h. For reasons of viability, the intention is to recruit two schools (one for intervention and another for control), from which a total sample size of 60 students is estimated.

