### Sample size, recruitment, participants and allocation

3.3

Prior to starting the present study, a power analysis was performed (G*Power 3; Heinrich-Heine-Universität, Düsseldorf, Germany) to calculate the adequate sample size (F-test, effect size = 0.25, α error = 0.05, power = 0.95). According to this calculation, the participation of 54 students is estimated. Being an experimental study, the sample is not large, however it has great power and can be representative of this group of students (30).

The eligible school directors will be invited to participate initially by e-mail and then they will be contacted a week later by telephone. A researcher will meet with all the interested directors to explain the requirements for participation in the study. Then, be organized a presentation day to explain the project to the teachers and students. Those who agree in include their schools in the study will receive a statement in simple language and a consent form to be signed. The recruitment lasts 2 months and will be during the year 2024. Finally, the study setting is two primary school in the city of Valparaíso, Chile.

Once the consent of the school authorities has been obtained, the consent in writing for the elementary classroom teachers to participate will be obtained, since the intervention will be part of the daily class activities. Afterward, all the children in the participating courses will receive a document with the information regarding the program containing a declaration in simple language, a consent form for the parents or guardians, and an assent form confirm the children’s participation. After this authorization, the ACTIVA-MENTE program will be carried out with all the children in the classes, but only data from children which the parents’ consent and their assent of participation will be compiled. The participation in the program will be volunteer and if the children are free to decide to give in the program whenever they want.

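### All analyses are stratified by sex with no pooled primary test described, although the sample size is for one comparison; run separately, each sex has about 70–75% power instead of 95%, and the primary activity variable is left open

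*Protocol article*

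**What the plan says.** Section 3.10 (Statistical analysis) describes multilevel mixed models for the effect of group on physical activity level, on-task behaviour and enjoyment, adjusted for baseline and grouped by class. It then adds: "All the analyses will be stratified by sex". No unstratified analysis is named as primary. The only decision criterion is a p value below 0.05.

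Section 3.3 (Sample size) gives one calculation, "F-test, effect size = 0.25, α error = 0.05, power = 0.95", and concludes that "the participation of 54 students is estimated". It does not mention sex. Section 3.2 plans for slightly more: "a total sample size of 60 students is estimated". Section 2 (Aim) and the main objective in Section 4 concern the effect in children as a whole.

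Section 3.7.1 names the primary outcome only as physical activity level. The accelerometer text, which sits under Section 3.7.3, adds: "The classification of the daily level of physical activity will be: sedentary, light, moderate, vigorous and moderate-vigorous, established from counts per minute". None of these classes is named as primary.

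**The concern.** The sample size and the analysis describe different trials. One comparison in 54 children was sized, but on the usual reading of stratified every comparison is made twice, each time in about half the children. The claim in Section 3.3 that the sample has great power would then apply to no planned analysis.

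The practical risk is a split result, with p below 0.05 in one sex and above it in the other. That is a common outcome of underpowered halves even when the programme works equally well in both. Without a pooled primary test, the plan does not say what the trial would then conclude.

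The open primary variable adds to this. The programme could shift one intensity class and not another, and a reader could not tell in advance which class decides the primary question.

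**Working it through.** **Inputs stated in the protocol article.** Effect size f = 0.25, α = 0.05, power 0.95, N = 54 (Section 3.3); two groups and a pre- and post-test design (Section 3.1); 60 students planned (Section 3.2).

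**Inputs not stated, assumed here.** The type of F-test, the number of measurements m and the correlation ρ. I took the repeated-measures within-between interaction with k = 2 groups, m = 2, ρ = 0.5 and sphericity, because this reproduces the stated figure. The sex split is also not given; I took 50:50, equal arms within each sex, and show a range.

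**Step 1: reproduce 54.** The noncentrality is λ = f²·N·m/(1−ρ), with df1 = (k−1)(m−1) and df2 = (N−k)(m−1).

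- N = 54: λ = 0.0625 × 54 × 2/0.5 = 13.5, df 1 and 52, power 0.950.
- N = 52: power 0.942.

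So 54 is the smallest even N that reaches 95%, an exact match. Other candidates do not match: the interaction with m = 3 needs 44 and with m = 4 needs 36; the between-group factor needs 158 (m = 2) or 142 (m = 3); a one-way ANOVA needs 210.

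**Step 2: the same test within one sex.**

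| Children in the stratum | λ | df | Power |
|---|---|---|---|
| 20 | 5.0 | 1, 18 | 0.56 |
| 24 | 6.0 | 1, 22 | 0.65 |
| 27 (half of 54) | 6.75 | 1, 25 | 0.704 |
| 30 (half of 60) | 7.5 | 1, 28 | 0.753 |
| 34 | 8.5 | 1, 32 | 0.81 |
| 36 | 9.0 | 1, 34 | 0.83 |

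An uneven split of 54 into 20 and 34 gives 56% and 81%. A split of 60 into 24 and 36 gives 65% and 83%. Keeping 95% within each sex would take 54 per sex, or 2 × 54 = 108 children.

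**Step 3: chance of a split verdict when the true effect is the same in both sexes.** Treating the two sexes as independent:

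- 27 per sex: 2 × 0.704 × (1 − 0.704) = 0.417, about 42%. Both significant: 0.704² = 0.496.
- 30 per sex: 2 × 0.753 × (1 − 0.753) = 0.372, about 37%.

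Boys and girls share schools, so the two results are not strictly independent. These figures show the order of magnitude.

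**Step 4: the primary variable.** Section 3.7.1 gives a label without a summary measure. Section 3.7.3 gives five classes, of which moderate-vigorous is the sum of two others. Section 3.10 models physical activity level in the singular. None of the three says which quantity enters the primary model.

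**The case against.** **The meaning of stratified.** Section 3.10 first describes a model for intervention against control and only then adds the sentence on sex. It could mean sex as a model term, or sex-specific results alongside the overall one. In either case the pooled test and its power remain. This stands as a limit: the power loss is conditional on separate models. That is the usual meaning, though, and the word all leaves no stated exception. If adjustment was meant, the sentence still needs rewording.

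**The power figures.** The test, the correlation and the sex split are inferred. The test that reproduces 54 is also not the planned baseline-adjusted mixed model with measurements at weeks 1, 3 and 6. This stands too. The 70% to 75% is the counterpart of the protocol's own 95%, not the true power of the trial, which also depends on clustering.

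**Ten primary tests.** A reader might infer that five classes in two sexes make ten tests at 0.05, with a false-positive risk near 1 − 0.95¹⁰ = 40%. The document does not support this. Section 3.7.3 says how counts are classified, not that each class is tested, and the classes are not independent. Multiplicity rules may also sit in an analysis plan that is not shown.

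**Total activity.** A reader might see a conflict between the Abstract, "The total physical activity will be measured with accelerometers (Actigraph wGT3X-BT", and Section 3.7.1, "The physical activity level will be only monitored during the school day". Total can mean all intensities within the monitored school day, so this is no contradiction.

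**Conclusion.** The point holds in conditional form. On the usual reading of Section 3.10, the analysis does not match the single comparison that Section 3.3 sized, and no stated aim calls for splitting by sex. Given separate models, an even sex split and the inferred test, power per sex is about 70% (27 children) to 75% (30 children) instead of 95%, before clustering; plausible uneven splits give 56% to 83%. With 27 per sex, a split verdict would arise about 42% of the time under identical true effects, and the plan does not say how to resolve it.

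Separately, and whatever stratified means, the primary activity variable is not fixed. No inflated error rate can be put on this, because the document does not say how many classes will be tested.

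This should be corrected. It does not invalidate the design.

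**What to change.** In Section 3.10, replace the sentence on stratification. State that the primary analysis is one pooled mixed model for the effect of group, with sex as a covariate, and that the group-by-sex interaction and sex-specific estimates are exploratory.

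In Section 3.7.1, name school-time moderate-to-vigorous activity as the single primary variable and make the other classes secondary. This follows from the document itself: the videos are built around that intensity (Section 3.5), and Section 4 states the expected benefit in daily minutes of it.

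The cost is a few sentences, with no added participants or measurements. The downside is that sex-specific results become exploratory. If they are in fact a main aim, Section 2 should say so and the sample size should be set for them: on the assumptions above, 108 children before clustering.
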